# Clinical impact of cardiac magnetic resonance in patients with suspected coronary artery disease associated with chronic kidney disease (AQUAMARINE-CKD study): study protocol for a randomized controlled trial

**DOI:** 10.1186/s13063-022-06820-w

**Published:** 2022-10-24

**Keywords:** Cardiac magnetic resonance, Coronary artery disease, Chronic kidney disease, Plaque imaging

## Abstract

**Background:**

Although screening for coronary artery disease (CAD) using computed tomography coronary angiography in patients with stable chest pain has been reported to be beneficial, patients with chronic kidney disease (CKD) might have limited benefit due to complications of contrast agent nephropathy and decreased diagnostic accuracy as a result of coronary artery calcifications. Cardiac magnetic resonance (CMR) has emerged as a novel imaging modality for detecting coronary stenosis and high-risk coronary plaques without contrast media that is not affected by coronary artery calcification. However, the clinical use of this technology has not been robustly evaluated.

**Methods:**

AQUAMARINE-CKD is an open parallel-group prospective multicenter randomized controlled trial of 524 patients with CKD at high risk for CAD estimated based on risk factor categories for a Japanese urban population (Suita score) recruited from 6 institutions. Participants will be randomized 1:1 to receive a CMR examination that includes non-contrast T1-weighted imaging and coronary magnetic angiography (CMR group) or standard examinations that include stress myocardial scintigraphy (control group). Randomization will be conducted using a web-based system. The primary outcome is a composite of cardiovascular events at 1 year after study examinations: all-cause death, death from CAD, nonfatal myocardial infarction, nonfatal ischemic stroke, and ischemia-driven unplanned coronary intervention (percutaneous coronary intervention or coronary bypass surgery).

**Discussion:**

If the combination of T1-weighted imaging and coronary magnetic angiography contributes to the risk assessment of CAD in patients with CKD, this study will have major clinical implications for the management of patients with CKD at high risk for CAD.

**Trial registration:**

Japan Registry of Clinical Trials (jRCT) 1,052,210,075. Registered on September 10, 2021.

**Supplementary Information:**

The online version contains supplementary material available at 10.1186/s13063-022-06820-w.

## Background

Computed tomography coronary angiography (CTCA) has been reported to be clinically beneficial in patients with stable chest pain due to coronary artery disease (CAD) [1, 2]. However, CTCA has disadvantages such as iodinated contrast agent use. In addition, the diagnostic accuracy of CTCA is limited by the amount of coronary artery calcification.

Coronary magnetic resonance angiography (CMRA) has emerged as an alternative imaging modality for visualizing coronary arteries [3, 4], and its prognostic value has been reported in patients with suspected CAD [5]. Moreover, the presence of high-intensity plaques (HIPs) detected with non-contrast T1-weighted imaging (T1WI) is associated with future coronary events [6]. Thus, the combination of whole-heart CMRA and non-contrast T1WI may be promising modalities for evaluating coronary artery stenosis and plaque characteristics simultaneously. However, no studies have investigated the clinical utility of these techniques for risk stratification and management of CAD. Moreover, no evaluations of the cost-effectiveness of CMRA plus non-contrast T1WI for investigating CAD have been performed to date.

Chronic kidney disease (CKD), defined as dysfunction of the glomerular filtration apparatus, is an independent risk factor for the development of CAD [7]. Although mortality risk in patients with CAD progressively increases with worsening CKD, the optimal imaging strategy for evaluating CAD in patients with CKD has been remained. Some patients with CKD have extensive calcification disproportionate to the severity of obstructive CAD [7, 8], which limits the diagnostic value of the CT calcium score. In addition, late-stage CKD has been associated with an increased risk of post-contrast acute kidney injury from CTCA. Thus, to date, myocardial perfusion scintigraphy and stress echocardiography can be used to assess obstructive CAD in patients with advanced CKD.

We will conduct a prospective multicenter randomized study called the Attempts at Plaque Vulnerability Quantification with Magnetic Resonance Imaging Using Non-contrast T1-weighted Technique (AQUAMARINE) [6]-CKD study to investigate the clinical impact of non-contrast T1WI and CMRA on management and risk stratification in patients with CKD and CAD or suspected CAD.

## Methods/design

### Aim

The aim of this study is to determine whether coronary HIPs visualized using non-contrast T1WI and coronary artery stenosis detected by CMRA can predict mortality and future coronary events in study participants receiving primary prevention for CAD.

### Study design

This is a multicenter, parallel-group, prospective randomized controlled, open-label, superiority trial to assess the impact of non-contrast T1WI and CMRA on the diagnosis and management of patients at high risk for CAD estimated based on CAD risk factor categories for a Japanese urban population (Suita score), which is composed of 8 coronary risk factor categories (Tables 1 and 2) [9, 10]. Eligible subjects are randomly assigned.

**Table 1 Tab1:** Suita score

Risk factor	Value	Score
Age (years)	35–44	30
	45–54	38
	55–64	45
	65–69	51
	> 70	53
Gender	Female	− 7
Current smoking	Yes	5
Diabetes mellitus	Yes	6
Blood pressure (mmHg)	Optimal (SBP < 120 and DBP < 80)	− 7
	Normal (SBP < 130, DBP < 85)	0
	High normal (SBP < 140 or DBP < 90)	0
	Stage I HTN (SBP 140–159 or DBP 90–99)	4
	Stage II–IV HTN (SBP 160–179 or DBP 100–109)	6
LDL-cholesterol (mg/dl)	< 100	0
	100–139	5
	140–159	7
	160–179	10
		11
HDL-cholesterol (mg/dl)	< 40	0
	40–59	− 5
	≥ 60	− 6
CKD	Stage I or II (eGFR > 60 ml/min/1.73 m^2^)	0
	Stage III (eGFR: 30–59 ml/min/1.73 m^2^)	3
	Stage 4 or 5 (eGFR < 30 ml/min/1.73 m^2^)	14

Weighted scoring of risk factors is used to categorize the 10-year risk of coronary heart disease. *CHD* coronary heart disease, *CKD* chronic kidney disease, *eGFR* estimated glomerular filtration rate, *DBP* diastolic blood pressure, *HDL* high-density lipoprotein, *HTN* hypertension, *LDL* low-density lipoprotein, *SBP* systolic blood pressure

**Table 2 Tab2:** Predicted probability of CHD in 10 years

Total Suita score	Estimated 10-year risk
< 35	< 1%
36–40	1%
41–45	2%
46–50	3%
51–55	5%
56–60	9%
61–65	14%
66–70	22%
> 71	> 28%

to the CMR group or the control group (allocation rate 1:1). The randomization stratified on the following variables: age, gender, presence or absence of type 2 diabetes mellitus, and CKD grade (Fig. 1).

**Fig. 1 Fig1:**
[figure not shown]
Trial design. CAD coronary artery disease, CKD chronic kidney disease, CMR cardiac magnetic resonance, CMRA coronary magnetic resonance angiography, ECG electrocardiogram, T1WI T1-weighted imaging

### Patient eligibility and recruitment

Patients aged 20 years or older with high cardiac risk estimated based on risk factor categories for a Japanese urban population (Suita score ≥66 points, corresponding to an estimated 10-year risk of CAD >22%) will be recruited from 6 institutions (Supplementary Figure 1). We will randomly assign 524 patients with CKD at high risk for CAD to evaluation with CMR (CMR group, 262 patients) at 6 institutions or to standard examinations that include stress myocardial scintigraphy (control group, 262 patients). Investigations, treatments, and clinical outcomes will be assessed over 1 year (short-term prognosis) and 3 years (long-term prognosis) (Fig. 1).

### Interventions

Eligible patients underwent non-contrast T1WI and CMRA (CMR group) or stress myocardial scintigraphy (control group) at each institution (Supplementary Figure 1). There is no anticipated harm and compensation for trial participation.

### Study procedures

Eligible patients will be randomly assigned to the CMR group or the control group. After each examination, follow-up will be performed until 144 weeks after allocation (Fig. 2).

**Fig. 2 Fig2:**
[figure not shown]
Sample timeline for enrollment, interventions, and assessments. CMR cardiac magnetic resonance, CMRA coronary magnetic resonance angiography, T1WI T1-weighted imaging

### Inclusion and exclusion criteria

#### Inclusion criteria

Study participants must meet all of the following criteria:Age of 20–85 yearsDiagnosis of hypertension, type 2 diabetes mellitus, non-cardiogenic cerebral infarction, peripheral arterial disease, carotid stenosis, aortic disease, or dyslipidemiaGrade ≥ 3 CKD with estimated glomerular filtration rate (eGFR) < 60 ml/min/1.73 m^2^ and very high risk for CAD, with a Suita score of ≥66 points with a predicted 10-year incidence of a coronary event of >22%Capable of visiting a study center on an outpatient basisCapable of providing written informed consent before study participation

#### Exclusion criteria

Individuals who meet any of the following criteria are ineligible for the study:Suspected acute coronary syndrome on assignmentAcute myocardial infarction (MI) according to the 4th universal definition [11]MI within 3 months prior to obtaining consent for study participationHistory of percutaneous coronary intervention (PCI) with stenting or coronary artery bypass grafting (CABG)Need for a coronary CT scanHemodialysis or peritoneal dialysisMR unsafe devices in the bodyHistory of cardiac surgery or thoracic surgery with sternotomyClaustrophobiaChronic atrial fibrillationFrequent atrial or ventricular extrasystoles on 12-lead ECG at restPhysician judgment that beta-blocker therapy would be inadvisable (e.g., due to arteriosclerosis obliterans with pain at rest, second-degree or higher atrioventricular block, sick sinus syndrome, or active bronchial asthma)Pregnancy, lactation, or being female and unable to consent to contraception during study participationParticipation in other clinical studies or are scheduled to participate in other clinical studies during this studyPrincipal investigator or sub-investigator judgment that study participation would be inappropriate for other reasonsPatient desire to discontinue study participation or withdraw consent

All eligible patients will be invited to enter the trial by their attending physician. Written informed consent will be obtained from patients willing to participate in the study.

### Outcomes

#### Primary endpoint

The primary outcome is a composite of cardiovascular events at 1 year after study examinations: all-cause death, death from cardiovascular disease, nonfatal MI, nonfatal ischemic stroke, and ischemia-driven* unplanned coronary intervention (PCI or CABG).

*Myocardial ischemia diagnosed with stress myocardial single photon emission computing tomography (SPECT), or invasive fractional flow reserve.

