### Statistical analysis

The study statistician ([name]) will supervise statistical analyses performed by the Department of Preventive Medicine and Epidemiology, National Cerebral and Cardiovascular Center. A full statistical analysis plan will be prepared separately.

All analyses will perform according to the intention-to-treat principle. Missing data will be removed from the analyses, except for data on deaths, which are censored at the time the patient is lost from the trial. Endpoints will be analyzed with the use of Cox regression models, adjusted for center and minimization variables, and cumulative event curves will be constructed.

Data are reported as means and standard deviations, medians and interquartile ranges, and hazard ratios or odds ratios with 95% confidence intervals, as appropriate. All statistical analyses will be performed with SPSS software (version 24.0; IBM Corp, Armonk, NY), Stata 15 (StataCorp, College Station, TX), or R software (version 3.4.3; R Foundation for Statistical Computing). All *p* values < 0.05 will be considered statistically significant.

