### Randomization

In this study, dynamic allocation will be used to ensure even allocation of factors that might affect the primary endpoint. After a study investigator confirms the eligibility of the patient and obtains consent for participation, dynamic allocation will be performed by the study investigator with respect to age, gender, presence or absence of type II diabetes, and CKD grade. Dynamic allocation will be performed at the allocation center (Medical Edge, Tokyo, Japan). The allocation table and the most recent breakdown of allocated subjects in each group will be used. A web-based system will be used to automatically register and allocate subjects on a 24-h basis without any human operators. After confirming that a patient meets all the eligibility criteria, the study investigator will enter the necessary items into the web-based system for registration. If there are no problems, the system will allocate the patient using the randomized minimization method based on allocation adjustment factors. The results of the allocation will be shown automatically on the website. The study investigator will start the examinations based on the notification and record them on the case report form (CRF) for each participant.

The minimization method will be employed for assignment to the study treatment in this study. The ratio of the two groups to be adjusted will be 1:1 for the CMR group and the control group. The group to which the new cases will be assigned will be determined using the following procedure. The number of subjects assigned to the category to which the patient belongs for all allocation factors in the control and CMR groups will be simply summed. If the calculated total numbers for the two groups are equal, a random assignment will be performed with the same probability (1/2). If they are not equal, the patient will be assigned to the smaller group with a probability of 1.

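### The 1-year and 3-year endpoints are timed from the study examination, which follows randomisation, while follow-up is timed from allocation and the analysis is called intention-to-treat

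*Protocol article*

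**What the plan says.** **Endpoint origin.** In the protocol article, the Primary endpoint section defines the outcome as a "composite of cardiovascular events at 1 year after study examinations". The Methods paragraph of the abstract uses the same origin, and the first item under Secondary endpoints applies it to the 3-year composite.

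**Order of steps.** Allocation comes first. The Randomization section describes web-based allocation and then says: "The study investigator will start the examinations based on the notification".

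**Follow-up.** The Study procedures section says: "After each examination, follow-up will be performed until 144 weeks after allocation". Follow-up is thus described as starting after the examination but ending at a time measured from allocation.

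**Analysis.** The Statistical analysis section says: "All analyses will perform according to the intention-to-treat principle". It also says: "Endpoints will be analyzed with the use of Cox regression models, adjusted for center and minimization variables". On incomplete data, it drops missing values, with an exception for deaths, where censoring applies when a patient is lost. A full statistical analysis plan is to be prepared separately.

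No section says how an event between allocation and examination is counted, or what time zero is given to a patient who is never examined.

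**The concern.** In a randomised trial the clock normally starts at randomisation, because only then are the groups comparable by design. Here it starts at a later event, and that event is a different test in each arm: CMR in one, stress scintigraphy in the other. Waiting times, withdrawals before the test and failures to complete it may therefore differ by arm, and the trial is open-label.

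Three things are at stake.

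- Events in randomised patients before their examination would not belong to the primary endpoint.
- Patients never examined would have no origin. The rule on removing missing data could then take them out altogether, leaving an analysis of examined patients, which is not intention-to-treat.
- The 3-year endpoint and the stated end of follow-up sit on different clocks and cannot both be met.

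**Working it through.** **Step 1. Set the sections side by side.**

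| Item | Origin stated | Section |
|---|---|---|
| Primary endpoint, 1 year | study examination | Abstract; Primary endpoint |
| Composite at 3 years | study examination | Secondary endpoints |
| Start of follow-up | after the examination | Study procedures |
| End of follow-up, 144 weeks | allocation | Study procedures |
| Outcomes over 1 and 3 years | none given | Patient eligibility and recruitment |
| Analysis set | intention-to-treat | Statistical analysis |

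A Cox model needs a time zero for every patient analysed. With the examination as origin, a patient who is never examined has none. The origin is stated three times, so it is not a single slip.

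**Step 2. Check the 3-year horizon.** 144 × 7 = 1008 days; 1008 / 365.25 = 2.76 years. Three years is 3 × 365.25 / 7 = 156.5 weeks. Follow-up from allocation falls 12.5 weeks short, plus whatever time passes before the examination.

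**Step 3. The plan's event rate.** The Sample size section uses an event rate of about 30% in patients with high-intensity plaque, 77% of events within 2 years, and an expected annual rate of 11.6%. Check: 0.30 × 0.77 / 2 = 0.1155, which agrees with 11.6% to rounding. The constant hazard is λ = −ln(1 − 0.116) = 0.1233 per year.

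**Step 4. Events before the examination (illustration).** The delay is not given, so 2 to 12 weeks is an assumption. For a wait of w weeks, the risk is q = 1 − exp(−λw/52), and the events per arm of 262 are 262q. If the same hazard applies after the examination, the 1-year count from examination is 262(1 − q) × 0.116. From allocation it is 262 × 0.116 = 30.4.

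| Wait | q | Uncounted events per arm | 1-year count from examination | Net change |
|---|---|---|---|---|
| 2 weeks | 0.47% | 1.2 | 30.2 | 0.1 |
| 4 weeks | 0.94% | 2.5 | 30.1 | 0.3 |
| 8 weeks | 1.88% | 4.9 | 29.8 | 0.6 |
| 12 weeks | 2.81% | 7.3 | 29.5 | 0.9 |

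For 4 weeks: 262 × 0.00944 = 2.5 patients are lost from the start, and the other 259.5 are still observed for a full year, giving 259.5 × 0.116 = 30.1.

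**Step 5. Lower event rate.** The 11.6% comes from patients with high-intensity plaque. The eligibility threshold of 22% over 10 years (coronary events only) gives λ = −ln(0.78)/10 = 0.0248 per year, or about 0.5 uncounted events per arm for a 4-week wait.

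**Step 6. Patients never examined.** The proportion is not given. Assuming 2%, 5% or 10% of 524, about 10, 26 or 52 patients would have no defined time zero.

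**The case against.** The strongest reply is that no section states an exclusion rule. The endpoint wording can be read as an assessment horizon, the analysis is declared intention-to-treat, and a separate statistical analysis plan would normally settle such handling. It stands that exclusion is the literal consequence of the definition and not a stated rule. But the assessment-horizon reading still gives the Cox model no origin for an unexamined patient. The origin is also positively stated, not left open: an analysis plan using allocation would depart from the published endpoint, and one using the examination would conflict with intention-to-treat.

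Several stronger readings that a reader might infer are not supported.

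- **Immortal time bias.** Both arms are tested and both clocks start at the test, so no event-free waiting time is credited to one arm. The risk is post-randomisation selection, which depends on delay or non-attendance differing by arm. The article gives no evidence on either.
- **Claustrophobia or arrhythmia removing CMR patients.** Claustrophobia, chronic atrial fibrillation, frequent extrasystoles and MR-unsafe devices are exclusion criteria, and eligibility is confirmed before allocation. Only new or unrecognised cases remain, with scheduling, withdrawal and death.
- **A loss of about 8% of control events** (2.5 of 30.4). This is a gross count. The window shifts and does not shrink, so the net change is about 0.3 events, or 1%.

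It also stands that the delay may be short. The examinations are started on notification of allocation, and the timeline figure, which is not available here, may give a window.

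**Conclusion.** The point holds as an inconsistency of time origin in the primary and 3-year endpoints. Followed literally, the definition leaves pre-examination events and never-examined patients outside an analysis called intention-to-treat, and it opens the comparison to selection after randomisation.

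A bias is possible but not demonstrated, and its size cannot be computed from the article. The 4-week wait is an assumption. The 0.3 net change per arm also assumes the plan's 11.6% rate and a hazard that is constant and equal before and after the examination. With short and equal waits and nearly complete attendance, the numerical effect would be small. It would matter more if the arms differed in delay or in the proportion never examined.

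The mismatch between 144 weeks from allocation and 3 years after the examination needs no assumption: no patient can reach the 3-year point within the stated follow-up.

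**What to change.** Define both endpoints as time from allocation to first event, through 1 year and through 3 years after allocation, in all randomised patients, including those never examined. Keep examination-based timing only as a sensitivity analysis. Align the abstract, Study procedures, Primary endpoint and Secondary endpoints sections, and reconcile 144 weeks with 3 years. Because the web system performs the allocation, its date should be available for every patient.

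The change is mostly wording, but it is not free.

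- Recruitment began in September 2021, so this is an endpoint and registry amendment in a running trial. It should be made before any comparison of outcomes.
- Counting from allocation includes time before the tests can act, which dilutes the effect somewhat. As an illustration, take a 4-week wait, a hazard ratio of 1 before the examination and 0.50 after it. The CMR arm's 1-year risk becomes 1 − exp(−0.1233 × [4/52 + 0.50 × 48/52]) = 6.4%, against 6.0% from examination. The risk ratio to 11.6% moves from 0.52 to 0.55. On a simple comparison of 1-year proportions with about 260 per arm, power falls from about 0.62 to 0.54. That is the effect of the strategies as randomised, and it is a reason to keep the wait short and similar in both arms.

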### Sample size

Based on the results of previous studies [6, 12, 14], we hypothesized that the 10-year probability of developing CAD would be ≥ 22% and that the effect of optimal drug therapy, such as a strong statin to reach the low-density lipoprotein (LDL) cholesterol control target and medications to reach the blood pressure control target, and the effect of screening with CMRA and non-contrast T1WI on patients with HIPs or coronary stenosis would result in 48–50% lower relative risk. The effect of early detection of coronary artery lesions (significant stenosis and unstable plaque) was estimated to result in a relative risk reduction of 48–50%. The SCOT-HEART study compared patients undergoing coronary CTCA versus conventional testing, similar to this study. The hazard ratio was 0.59 in the CTCA group compared with the conventional test group. We assumed that CTCA in the SCOT-HEART study [1, 15, 16] did not assess plaque instability and that CMR with analysis of HIPs could assess plaque instability better than CTCA alone. In a previous study [14], 77% of all cardiovascular events occurred within 2 years, and the event rate for HIP with signal intensity > 1.4 was approximately 30%; thus, an annual event rate of 11.6% was expected. Based on additional assumptions about an enrollment period of 3 years and a follow-up period of 3 years, power of 0.8, and two-sided *p* value of 0.05, a total of 524 patients would be needed with the dropout rate set at 5%.

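### The sample size rests on an effect argued from coronary lesions, with no endpoint named for it, so the stated power of 0.8 is not shown for the 1-year composite that counts every death

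*Protocol article*

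**What the plan says.** **Endpoint.** The Primary endpoint section sets the time point at 1 year after the study examinations. It lists "all-cause death, death from cardiovascular disease, nonfatal MI, nonfatal ischemic stroke" and ischaemia-driven unplanned PCI or CABG. The Methods paragraph of the Abstract words the death items differently: "all-cause death, death from CAD, nonfatal myocardial infarction". Both places describe the whole as a composite of cardiovascular events.

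**Effect used for sizing.** The Sample size section opens with "the 10-year probability of developing CAD would be" at least 22%. It attributes the benefit to "the effect of optimal drug therapy, such as a strong statin to reach the low-density lipoprotein (LDL) cholesterol control target", to blood-pressure medication, and to screening of patients with high-intensity plaques or stenosis. It then says that "early detection of coronary artery lesions (significant stenosis and unstable plaque) was estimated to result in a relative risk reduction" of 48–50%. As a benchmark it cites a CT angiography trial: "The hazard ratio was 0.59 in the CTCA group compared with the conventional test group". It names no endpoint for the 48–50% or for the 0.59.

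**Rate and design.** The annual rate of 11.6% comes from an earlier study's figures for all cardiovascular events and for patients with plaque signal above 1.4. The other inputs are 3 years of enrolment, 3 years of follow-up, power 0.8, "two-sided *p* value of 0.05" and 5% dropout. The result is 524 patients, 262 per arm.

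**The concern.** A power statement belongs to one endpoint, with its own event rate and its own effect. Here the effect is argued through coronary lesions, while the tested endpoint also counts every death, whatever its cause. The inclusion criteria admit patients up to age 85 with CKD grade 3 or higher, so some deaths from non-cardiovascular causes must be expected. Neither lesion detection nor the lipid and blood-pressure treatment named in the Sample size section is offered as a way to prevent those deaths. They add about equally to both arms and pull the composite hazard ratio towards 1. The sizing makes no visible allowance for this: it assumes a stronger effect (0.50–0.52) than its own benchmark (0.59).

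At stake is how a null primary result would be read. If the trial is believed to have 80% power for this composite, a null result counts as evidence against the imaging strategy. If power is materially lower, it does not.

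**Working it through.** **Inputs from the Sample size section.** Two-sided alpha 0.05 (z = 1.960); power 0.8 (z = 0.842); relative risk or hazard ratio 0.50–0.52; control rate 11.6% per year (0.30 × 0.77 / 2 = 0.1155); 262 per arm; 5% dropout, so 262 × 0.95 ≈ 249 evaluable per arm.

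**Assumed input.** s is the share of control-arm composite events that the strategy does not change. The document gives no value; 10%, 20% and 30% are shown.

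**1. The plan's own figure.** 524 was not reproduced from the stated inputs.
- 1-year proportions, pooled-variance formula: 11.6% v 5.8% needs 740 patients, or 779 with dropout (740 / 0.95). Relative risk 0.52 needs 812, or 855 with dropout.
- Survival calculation (Schoenfeld), fixed 3 years: events = 4(1.960 + 0.842)² / (ln HR)², which is 66 at HR 0.50 and 74 at 0.52. With hazard 0.116 the mean event probability is (0.294 + 0.160)/2 = 0.227 at HR 0.50, giving 291 patients. HR 0.52 gives 322. Both are before dropout.
- 3 years of accrual plus 3 years of follow-up: 209–231 patients before dropout.

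**2. Power at 1 year with no dilution.** Power = Φ[(d√n − 1.960·√(2p̄(1−p̄))) / √(p₁(1−p₁) + p₂(1−p₂))], with n = 249 and d = p₁ − p₂.
- Relative risk 0.50: p₁ = 0.116, p₂ = 0.058, d√n = 0.915. (0.915 − 1.960 × 0.399)/0.397 ≈ 0.34, so power is 0.63.
- Relative risk 0.52: p₂ = 0.0603, power 0.59.

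**3. Dilution.** Composite relative risk R = s + (1 − s) × 0.50, with the composite control rate held at 11.6%. The 1-year column uses the formula in step 2. The 3-year column uses Φ[(√D/2)·|ln R| − 1.960], where D is the expected number of events in 498 patients at hazard 0.116.

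| s (assumed) | R | Power, 1 year | D, fixed 3 years | Power, fixed 3 years |
|---|---|---|---|---|
| 0 | 0.50 | 0.63 | 113 | 0.96 |
| 10% | 0.55 | 0.53 | 117 | 0.90 |
| 20% | 0.60 | 0.43 | 120 | 0.80 |
| 30% | 0.65 | 0.34 | 124 | 0.67 |

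Starting from 0.52, power at s = 20% is 0.40 at 1 year and 0.76 over 3 years.

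**4. Sensitivity.** If the unaffected events come on top of an 11.6% rate of preventable events, the loss is smaller. Over a fixed 3 years at HR 0.50 and s = 20%, power is 0.87 instead of 0.80. At 1 year, by the Schoenfeld formula, it falls from 0.61 to 0.47, against 0.40 when the total rate is held fixed.

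**The case against.** The strongest reply is that the document does not say the 48–50% is an effect on coronary events. Its endpoint is unnamed, as is that of the 0.59 benchmark, and the study behind the rate is described in terms of all cardiovascular events. The assumed effect may already be meant for a broad composite. This stands: a reader might infer that the wrong endpoint was used, but the text supports only that the endpoint is not stated.

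Second, a reader might treat ischaemic stroke and cardiovascular death as unaffected. The stated mechanism includes statin and blood-pressure treatment, so the document gives no basis for assuming no effect on them. Only non-cardiovascular death is clearly outside it, which makes the lower shares in the table the safer ones.

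Third, one might hold the trial at the 65 or so events that give 80% power at HR 0.50 and conclude that dilution of 20–40% cuts power to 54–30%. Those figures do not describe this trial. At HR 0.50 and hazard 0.116 the design yields about 41 events at 1 year or about 113 over 3 years. Over a fixed 3 years, 0.8 survives an unaffected share of up to about 20% (HR 0.50) or 17% (HR 0.52); with 3 + 3 years, up to about 30% or 27%. That reserve is not available to a 1-year endpoint.

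Finally, counting all deaths looks deliberate, since the Aim names mortality. The lack of a coronary-only secondary endpoint is not a defect either: such analyses are commonly left to the statistical analysis plan, which the article says will be prepared separately.

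**Conclusion.** The point holds in this form: the Sample size section states neither the endpoint behind its effect nor an expected effect for the 1-year composite, so the power of 0.8 is not shown for the endpoint that will be tested. The direction is secure, because any non-cardiovascular deaths move the composite hazard ratio towards 1. The size is conditional. Taking the stated inputs at face value, 1-year power is about 0.59–0.63 with no dilution. At relative risk 0.50 it is 0.53–0.34 if 10–30% of control events are unaffected, a share that is assumed throughout.

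Most of the shortfall from 0.8 at 1 year comes from a separate matter: the sizing uses 3 years of follow-up while the primary endpoint is at 1 year. Dilution adds to that shortfall. The calculations also accept the 11.6% as given, although it derives from a subgroup with high plaque signal.

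The different cause-specific death items in the Abstract and the Primary endpoint section have no numerical effect, because all-cause death covers both. That correction is editorial.

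**What to change.** In the Sample size section:
- name the endpoint to which the 48–50% and the 11.6% apply;
- state the hazard ratio expected for the 1-year composite, with an explicit allowance for non-cardiovascular death;
- restate the power of 524 patients on that basis, over a range of unaffected shares.

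Keep all-cause death, which is robust in an open-label trial. As an editorial correction, delete the redundant cause-specific death item so that the Abstract and the Primary endpoint section agree.

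Optionally, add a coronary composite (coronary death, MI, ischaemia-driven revascularisation) as a secondary endpoint. Attach the 48–50% to it only if the sponsor confirms that this is the figure's source endpoint. It would need coronary death to be classified separately, which the article does not establish.

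The cost of the required changes is wording and a short recalculation, with no new data. The stated power for the primary endpoint will probably look less favourable.
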